### Outcome measures

Serum levels of the pancreatic tumor markers carbohydrate antigen 19-9 (CA19-9) and carcinoembryonic antigen (CEA), and routinely performed cross-sectional imaging (computed tomography or magnetic resonance imaging), will be monitored and assessed as parameters for evaluating disease status. Staging examinations will take place every three months after study inclusion during the treatment course with cytoreductive chemotherapy (Figure 1). The total concentration of isothiocyanates (sulforaphane) in urine will serve as a monitoring parameter for the evaluation of patient compliance. Additionally, the overall survival rate will be documented.To evaluate the quality of life of the study participants, questionnaires (European Organisation for Research and Treatment of Cancer (EORTC) Quality of Life Questionnaires (QLQ-PAN26, QLQ-C30) will be completed at every follow-up visit (3, 6, and 12 months after patient inclusion), in addition to the evaluation of a patient diary kept to document the regular intake and amount of the test substances, and any observable side effects (adverse or otherwise) (Figure 1). If outcome differences between the verum and the placebo groups are detected after completion of the POUDER trial, statistical analyses will be performed in order to generate a hypothesis for a confirmatory trial on this topic.

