## Methods/Design

The ethics committee of the University of Heidelberg has approved the POUDER trial as a monocentric, prospective, randomized, placebo-controlled clinical pilot study with two parallel groups (placebo versus verum) and provided the trial ethical approval (reference S-347/2009). Forty eligible patients receiving palliative chemotherapy, who meet the inclusion criteria (Table 1), with advanced, non-resectable PDA treated at the European Pancreas Center in Heidelberg, will be enrolled after signing informed consent. Approximately 15 to 20 PDA patients who meet the study inclusion criteria are treated in the outpatient department of the European Pancreas Center per month. Therefore, a short recruitment period of 3 to 4 months is expected. Exclusion criteria are a known intolerance to broccoli or its ingredients, impaired mental status, language problems, or a refusal of participation. Due to the nutrition supplemental character of the trial, sufficient oral intake is a prerequisite for inclusion in the study that is, the patients should not have symptoms or signs of indigestion or problems with the passage of food (nausea, vomitus, presence of nasogastric tube) (Table 1).

**Table 1 T1:** Trial inclusion and exclusion criteria

**Inclusion criteria**	**Exclusion criteria**
Patients ≥18 years	Intolerance to broccoli or its ingredients
Advanced, surgically non-treatable PDA^a^	Impaired mental status or language problems/barriers
Written informed consent	
Intact gastric emptying	
Palliative chemotherapy	

^a^Patients who receive surgical exploration, intraoperative biopsy, and/or palliative bypass interventions (bileodigestive anastomosis and/or gastroenterostomy because of preoperative cholestasis or impaired gastric emptying due to a tumor-mass effect) will be included in this trial. PDA, pancreatic ductal adenocarcinoma.

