Biochemical analysis of serum tumor markers will take place during the first visit and for all subsequent visits, scheduled at 3-month intervals, until the end of the follow-up period. Diagnostic imaging (CT/MRI scans) will be routinely performed during the oncological follow up of the patients. If the findings of the imaging diagnostic are available, they will be included as monitoring parameters and, together with the tumor markers, will provide insight into the status of the disease. The last visit will be scheduled one year after the beginning of the trial and will serve to investigate the clinical status of the patient, as well as to compile all efficacy and safety data.

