### Randomization and blinding

A 1:1 randomization will be performed and patients will be assigned with a randomization number. In case there are dropouts, these patients will be replaced and the new patients will be assigned in an identical manner. If a patient drops out of the study at month 6 due to his/her own decision, the patient data will be removed from the trial completely, including any data generated prior to the withdrawal. If a patient passes away during the first 6 months, the data will be used. If the urine probes reveal that a patient from the broccoli sprouts group did not consume the broccoli sprouts daily or if a patient from the placebo group had a high dietary intake of isothiocyanates, the data from these patients will not be used, but the patient will be replaced by a new patient, even if a patient drops out between months 9 to 12. This case will extend the duration of the study. Randomly generated numbers will be allocated to the two groups in balanced permuted blocks using a number generator (validated software, SAS). In order to avoid any possibility of predicting the group allocation, the length of the blocks will be fixed in a separate document and this information will be withheld from the study site. A data sheet that links the group allocation with the randomized number of the patient will be sealed in pre-produced, non transparent envelopes labeled with the arbitrary patient numbers and these envelopes will be used in consecutive order. In order to be able to perform a retrospective control of the compliance to randomization, basic patient data, including the day on which the patient’s number was assigned, will be noted on the data sheet. After completing the trial, all unopened envelopes will be delivered to the data management center for comparison to the allocated, randomized patient numbers and examination and evaluation of the thoroughness of the trial.

The investigators, patients, and assessors of the POUDER trial will be blind to the patients’ study treatment courses. The principal investigator (PI) will be provided with a set of sealed envelopes containing information on patients’ trial drugs, one for each patient number. These envelopes are to be opened only under imperative circumstances (medical indication to know the substance in use by the subject).

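### CA 19-9 is read as disease status in a trial that admits patients bypassed for cholestasis, so marker change may partly reflect bile drainage: noise and chance imbalance between arms, not systematic bias

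*Protocol article*

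**What the plan says.** Under Outcome measures, the markers, introduced as "Serum levels of the pancreatic tumor markers carbohydrate antigen 19-9 (CA19-9) and carcinoembryonic antigen (CEA", are listed together with routine cross-sectional imaging and "will be monitored and assessed as parameters for evaluating disease status". Trial interventions sets the schedule: "Biochemical analysis of serum tumor markers will take place during the first visit and for all subsequent visits, scheduled at 3-month intervals". Imaging is conditional: "If the findings of the imaging diagnostic are available, they will be included as monitoring parameters and, together with the tumor markers" give the picture of disease status.

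Footnote a of Table 1 (Methods/Design) states that patients with "palliative bypass interventions (bileodigestive anastomosis and/or gastroenterostomy because of preoperative cholestasis or impaired gastric emptying due to a tumor-mass effect) will be included". Neither Table 1 nor the sampling schedule sets a condition on biliary status or on the time between drainage and the first sample.

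Under Randomization and blinding, "A 1:1 randomization will be performed and patients will be assigned with a randomization number"; permuted blocks are used and no stratification factor is named. Data management and statistical analysis compares continuous parameters by t-test or Mann-Whitney test, with descriptive P-values and 95% confidence intervals, and names no covariate. The group size is 20, without a calculation. The principal objective is whether the daily intake is possible. Differences seen between the groups are to be used to form a hypothesis for a confirmatory trial.

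**The concern.** The article fixes both halves of the problem: who enters, and how the marker is read. CA 19-9 can rise with biliary obstruction whatever the tumour is doing. That link is general laboratory knowledge; the article does not mention it, and it is taken here as a premise.

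Given the premise, there are two routes to a misleading reading. A patient first sampled while cholestasis is still resolving after a bypass would show a fall at month 3 that looks like a marker response. A patient whose biliary passage closes again during the year would show a rise that looks like progression.

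Imaging is an incomplete safeguard, because it is used only when available while the markers are scheduled at every visit. CEA does not show whether a CA 19-9 change came from drainage. What is at stake is the marker signal that may feed the planned confirmatory trial, not the feasibility objective.

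**Working it through.** The article gives no effect size, SD or power for CA 19-9, so there is no figure of its own to reproduce. What follows is a sensitivity check.

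**Inputs.** From the article: 20 patients per group, 1:1 allocation, unadjusted comparison. Assumed, because the article is silent: share p of patients whose marker is affected, 10% to 50%; fold inflation k of the baseline, 2 to 10; extra marker change s in affected patients, 0.5 to 2 residual SDs; SD of the log change, 0.75 to 1.5.

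**1. How likely is a chance imbalance?** Take the difference of two independent Binomial(20, p) counts and find the probability that it is at least 4 patients (20 percentage points) in either direction:

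| p | 0.1 | 0.2 | 0.3 | 0.4 | 0.5 |
|---|---|---|---|---|---|
| probability | 6% | 16% | 23% | 26% | 27% |

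**2. What would such an imbalance do?** Suppose 8/20 in one arm and 4/20 in the other have a baseline inflated k-fold that later normalises fully, with no treatment effect. The difference in proportions is 0.40 − 0.20 = 0.20, so the spurious ratio of geometric-mean change is k^0.20:
- k = 2: 1.15 (log 0.14)
- k = 3: 1.25 (log 0.22)
- k = 10: 1.58 (log 0.46)

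**3. How does that compare with sampling error?** The standard error of the between-arm difference is SD × √(2/20) = 0.316 × SD, that is 0.24 to 0.47 for SD 0.75 to 1.5. The 2-fold shift is 0.3 to 0.6 SE and the 3-fold shift 0.5 to 0.9 SE. Only the 10-fold shift reaches about 1.0 to 1.9 SE.

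**4. What is lost if the arms are balanced?** The SD grows to √(1 + p(1 − p)s²). Without any drainage effect, 20 per arm gives 80% power for (1.960 + 0.842) × √(2/20) = 0.886 SD. This serves only as a measure of precision, since the trial is not powered. For that same difference:

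| p | s = 0.5 | s = 1 | s = 2 |
|---|---|---|---|
| 0.1 | 0.79 | 0.77 | 0.67 |
| 0.3 | 0.78 | 0.72 | 0.54 |
| 0.5 | 0.78 | 0.71 | 0.51 |

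**5. Change within one arm.** Randomisation does not cancel the effect here. If 30% of an arm (12 of 40, the overall share in step 2) have an inflated baseline that normalises, the arm's geometric mean is multiplied by k^−0.30: 0.81, 0.72 or 0.50 for k = 2, 3 or 10. That is an apparent fall of 19%, 28% or 50% with no change in tumour.

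The effect runs from negligible to substantial over these ranges, and nothing in the article shows where this trial falls.

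**The case against.** **Bias between arms.** A reader might infer that the marker comparison is biased towards one treatment. The article does not support that: allocation is 1:1 and blinded, so drainage affects both arms equally in expectation. The later removal and replacement of patients, described under Randomization and blinding, weakens that protection, but nothing shows that it acts through cholestasis.

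**Drainage as an established cause.** A reader might also infer that CA 19-9 change in this trial does measure drainage. The footnote calls the cholestasis preoperative, the bypass is meant to relieve it, and it may have resolved by the first visit. The footnote also covers exploration, biopsy and gastric bypass, so the biliary share is unknown. What remains is that nothing shown requires resolution before the first sample, and obstruction may recur within the year.

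**Missing bilirubin rule.** A condensed article may leave this to the full protocol or analysis plan, so its absence is not itself an error. Nor can one say that drainage and tumour change could never be separated afterwards: bilirubin is a routine blood value during chemotherapy and might be retrieved from records, though not necessarily from the same draw. The point rests on what the article does fix: the entry rule, the unqualified reading of the marker and the unadjusted comparison.

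**Little weight on the marker.** It is read with CEA and, when available, imaging; feasibility is the principal objective; P-values are descriptive. Chance imbalance at 20 per group affects every prognostic factor. This is fair and keeps the point small. The 8 against 4 scenario is a chosen one, and its 2- and 3-fold shifts lie below one standard error.

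**Conclusion.** The point holds in a limited form. Marker change may partly reflect biliary drainage or re-obstruction in a group of patients that the article itself names. Between arms this means added noise and possible chance imbalance; change within an arm is more exposed.

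The size in this trial is unknown. The figures above depend on the assumed share, fold inflation and SD. They also assume that every affected patient starts inflated and normalises fully, and geometric-mean ratios do not describe a Mann-Whitney comparison. The conclusion rests further on the premise that cholestasis raises CA 19-9, which comes from outside the article.

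This is a cheap improvement to an exploratory outcome. It does not threaten the feasibility objective.

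**What to change.** 1. Record total bilirubin from the same draw as every CA 19-9 sample.
2. Keep all values in the main marker comparison. Analyse log CA 19-9 adjusted for baseline CA 19-9 and baseline bilirubin.
3. Prespecify a sensitivity analysis restricted to patients with normal bilirubin at baseline.
4. Add a second sensitivity analysis, labelled exploratory, that sets aside later values drawn with raised bilirubin. It should not be the main comparison: it conditions on something measured after randomisation, and re-obstruction may itself reflect tumour growth, so the discarded values may be informative.

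The cost is one CRF field and a few lines of analysis wording, with fewer values in the two sensitivity sets. Nothing in patient management changes.

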**Figure 1 F1:**
[figure not shown]
**Flow chart of the POUDER-Trial.** PDA, pancreatic ductal adenocarcinoma: AE, adverse event: SAE, serious adverse event: CT, computed tomography; MRI, magnetic resonance imaging. Tumor markers: CEA and CA 19-9.

Biochemical analysis of serum tumor markers will take place during the first visit and for all subsequent visits, scheduled at 3-month intervals, until the end of the follow-up period. Diagnostic imaging (CT/MRI scans) will be routinely performed during the oncological follow up of the patients. If the findings of the imaging diagnostic are available, they will be included as monitoring parameters and, together with the tumor markers, will provide insight into the status of the disease. The last visit will be scheduled one year after the beginning of the trial and will serve to investigate the clinical status of the patient, as well as to compile all efficacy and safety data.

### Randomization and blinding

A 1:1 randomization will be performed and patients will be assigned with a randomization number. In case there are dropouts, these patients will be replaced and the new patients will be assigned in an identical manner. If a patient drops out of the study at month 6 due to his/her own decision, the patient data will be removed from the trial completely, including any data generated prior to the withdrawal. If a patient passes away during the first 6 months, the data will be used. If the urine probes reveal that a patient from the broccoli sprouts group did not consume the broccoli sprouts daily or if a patient from the placebo group had a high dietary intake of isothiocyanates, the data from these patients will not be used, but the patient will be replaced by a new patient, even if a patient drops out between months 9 to 12. This case will extend the duration of the study. Randomly generated numbers will be allocated to the two groups in balanced permuted blocks using a number generator (validated software, SAS). In order to avoid any possibility of predicting the group allocation, the length of the blocks will be fixed in a separate document and this information will be withheld from the study site. A data sheet that links the group allocation with the randomized number of the patient will be sealed in pre-produced, non transparent envelopes labeled with the arbitrary patient numbers and these envelopes will be used in consecutive order. In order to be able to perform a retrospective control of the compliance to randomization, basic patient data, including the day on which the patient’s number was assigned, will be noted on the data sheet. After completing the trial, all unopened envelopes will be delivered to the data management center for comparison to the allocated, randomized patient numbers and examination and evaluation of the thoroughness of the trial.

The investigators, patients, and assessors of the POUDER trial will be blind to the patients’ study treatment courses. The principal investigator (PI) will be provided with a set of sealed envelopes containing information on patients’ trial drugs, one for each patient number. These envelopes are to be opened only under imperative circumstances (medical indication to know the substance in use by the subject).

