**Methods and study design:**

The study is designed as a prospective randomized, double-blinded pilot trial with a treatment and a placebo-controlled arm in a single center setting. A total number of forty patients (18 years or older) in two parallel groups with advanced, surgically non-resectable PDA under palliative chemotherapy are planned for recruitment. Patients in the treatment group will receive fifteen capsules of the study substance per day (90 mg of active sulforaphane) during the chemotherapy treatment course. Patients in the placebo group will receive the same capsule size and portion distribution with inactive substances (mainly methylcellulose). The follow-up duration is one year. Feasibility of the study substance, adverse effects, and patient compliance, as well as levels of serum tumor markers (CEA, CA 19-9), quality of life, and patient overall survival rates will be assessed at defined points of time.

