### Data management and statistical analysis

The trial investigator or a designated representative (sub-investigator) will document all data acquired during the trial in a case report form (CRF) on the day of the routine visit. All missing or inconsistent data will be reported and inferred. Upon completion, all CRFs must be officially reviewed and signed by either the investigator named in the trial protocol or by a designated sub-investigator. In order to assure the highest data quality and accurate transfer from the CRF to the database, a double data-entry method will be performed. After completing the trial, the PI will retain the original CRFs.

Totality, validity, and plausibility of the data will be examined by validating programs that will generate queries that must be clarified by the investigator. All findings, both clinical and overall survival, imaging of disease stages, quality of life, and biochemical analyses will be noted in the subject’s CRF.

As this is a pilot study, no sample size calculation was performed. A sample size of 20 patients per study group has been deemed sufficient for the study objectives. The sample size of 20 patients per group is speculative at this time and it is based on comparable patient numbers used in similar ongoing and recently completed patient studies with broccoli sprout extracts. For example, the Pittsburgh pilot study evaluating sulforaphane in atypical nevi-precursor lesions enrolled 18 patients (http://clinicaltrials.gov/ct2/show/NCT01568996?term=NCT01568996&rank=1) and another study performed at OHSU Knight Cancer Institute for examination of sulforaphane in treating patients with recurrent prostate cancer (http://clinicaltrials.gov/ct2/show/record/NCT01228084?term=sulforaphane&rank=1) enrolled 20 patients.

Depending on data characteristics, descriptive statistics of the monitored parameters will be presented as mean values and SD or median values and IQR. Descriptive *P*-values of the *t*-test or the Mann-Whitney *U*-test comparing the treatment groups will be given, together with the corresponding 95% CI. Categorical parameters will be presented as relative and absolute frequencies, and comparisons will be performed using the Fisher exact test.

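### Uncapped replacement of dropouts restores 40 in total but does not guarantee 20 per group, substitutes the patients a feasibility pilot most needs to count, and extends the trial without a bound

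*Protocol article*

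**What the plan says.** On size, the abstract plans "A total number of forty patients (18 years or older) in two parallel groups". The Data management and statistical analysis section adds "A sample size of 20 patients per study group has been deemed sufficient for the study objectives", but also says "As this is a pilot study, no sample size calculation was performed" and "The sample size of 20 patients per group is speculative at this time".

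On allocation, the Randomization and blinding section says "A 1:1 randomization will be performed and patients will be assigned with a randomization number". It specifies balanced permuted blocks of undisclosed length, envelopes opened consecutively, and blinded investigators, patients and assessors.

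On replacement, the same section says "In case there are dropouts, these patients will be replaced and the new patients will be assigned in an identical manner". It also replaces verum patients whose urine shows that they did not take the sprouts every day, and placebo patients with a high dietary intake of isothiocyanates. Neither group's data are used. Replacement applies "even if a patient drops out between months 9 to 12. This case will extend the duration of the study". Data of patients who leave at month 6 by their own decision are removed entirely; data of patients who die in the first 6 months are kept.

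On timing, Methods/Design reports 15 to 20 eligible patients a month and concludes: "Therefore, a short recruitment period of 3 to 4 months is expected". Follow-up lasts one year (Trial interventions).

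The Trial objectives section makes the principal objective whether 15 capsules a day can be taken.

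**The concern.** A replacement that takes the next number on a 1:1 list is as likely to join the other arm as the arm that lost a patient. The total is refilled, but the balance is not. If one arm loses more patients, it ends up smaller. The urine rule makes unequal loss plausible, because failing to take the capsules leads to replacement in the verum arm but not in the placebo arm.

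Two further consequences matter more than balance. First, in a feasibility trial, stopping or not taking the capsules is the outcome of interest, yet the rule substitutes another patient for each one who does so. Second, a loss recognised at month 6 or later cannot be replaced within a recruitment period of 3 to 4 months, and each new patient needs a full year of follow-up.

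**Working it through.** **Inputs from the article:** 40 patients, 20 per group, 1:1 permuted blocks, consecutive envelopes, 15 to 20 eligible patients a month, one year of follow-up, last urine sample at month 6. **Assumed, because the article does not give them:** loss rates by arm, block length (4; 8 gives similar results), and that enrolment continues until 40 patients are retained in total.

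**1. The plan's own figures.** The 20 per group has no calculation behind it, so there is nothing to reproduce. The recruitment period can be checked. If every eligible patient joined, 40 would take 40/20 = 2.0 to 40/15 = 2.7 months. Three to four months supply 3 × 15 = 45 to 4 × 20 = 80 eligible patients, so participation of 40/80 = 50% to 40/45 = 89% is needed. The expectation is coherent for 40 patients without replacement.

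**2. Retained split.** With loss rates v (verum) and p (placebo), the expected verum size among 40 retained is close to 40 × (1 − v) / [(1 − v) + (1 − p)]. The number randomised is close to 40 / [1 − (v + p)/2]. For 30% and 10%: 40 × 0.7/1.6 = 17.5 verum, and 40/0.8 = 50 randomised. A simulation of 20,000 trials with blocks of 4 agrees:

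| Assumed loss, verum / placebo | Mean retained, verum / placebo | Exactly 20/20 | Mean randomised |
|---|---|---|---|
| 0% / 0% | 20 / 20 | 100% | 40 |
| 10% / 10% | 20 / 20 | 38% | 44.5 |
| 20% / 20% | 20 / 20 | 27% | 50.0 |
| 30% / 30% | 20 / 20 | 22% | 57.2 |
| 20% / 10% | 18.8 / 21.2 | 21% | 47.1 |
| 30% / 10% | 17.5 / 22.5 | 6% to 7% | 50.0 |
| 40% / 10% | 16.0 / 24.0 | 1% | 53.3 |

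Under equal loss the departures are small: the verum arm is within one patient of 20 in 85%, 70% and 61% of runs at 10%, 20% and 30% loss.

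**3. Precision.** Relative to 20/20, the standard error of a difference in means changes by √(1/a + 1/b) / √(1/20 + 1/20).
- 17.5/22.5: √0.1016 / √0.1 = 1.008, an increase of 0.8%.
- 16/24: 1.021, an increase of 2.1%.
- For an estimate within the verum arm alone, 16 instead of 20 patients gives √(20/16) = 1.118, about 12% more.

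**4. What the retained set shows about feasibility.** Suppose 30% of verum patients withdraw at month 6 or fail the urine check. Of 20 randomised, 20 × 0.7 = 14 would meet those criteria, a proportion of 70%. In the set left after replacement, with the lost patients' data removed or unused, all of the roughly 17.5 verum patients meet them by construction.

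**5. Timing.** Without replacement, a patient enrolled at month 4 finishes at 4 + 12 = 16 months. If the very first patient is lost at month 6, the replacement finishes at 6 + 12 = 18 months or later; if lost at month 12, at 24 months or later. If a patient enrolled at month 4 is lost at month 12 of follow-up, the replacement finishes at 4 + 12 + 12 = 28 months or later. The article sets no limit on repeating this.

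**6. Other readings of the replacement sentence.**
- *Same arm as the lost patient.* This holds 20/20, but the replacement is not randomised and whoever assigns it must know the group. It does not change the timing.
- *Continue until each arm reaches 20.* At 30%/10% loss this needs about 20/0.7 = 28.6 verum patients. By then about 28.6 × 0.9 = 25.7 placebo patients are retained, so the total is near 46 rather than 40.

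**The case against.** A reader might infer that the stated 20 per group and the 3 to 4 month recruitment period are simply not delivered. The documents do not support that.

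- The shortfall depends on loss rates that the article does not give. With no loss the split is exact, and with equal loss its mean stays 20/20. The direction is also open: the article expects few adverse events, and placebo patients can be removed too.
- Twenty per group is not the only size stated. The abstract and Methods/Design give 40, which replacement does restore. The 20 is uncalculated, is called speculative, and supports only descriptive P-values, so no power claim fails.
- The recruitment period is an expectation that fits the stated patient flow, and the article itself says that late replacement will lengthen the study. This is a disclosed extension without a bound, not a contradiction. The 28-month figure needs a last-enrolled patient to be lost at the very end of follow-up.
- Taking the next number on the list is an inference from the surrounding text, not a stated rule. A cap on replacements may stand in the full protocol, which an article condenses.
- Removing replacement leaves fewer completers: at 30%/10% loss, 14 and 18 instead of 17.5 and 22.5.

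All of this stands and limits the point on numbers. It does not answer the other two: substituting the patients who stop works against a feasibility objective, and the article describes late replacement as a rule with no end. The last bullet is a real cost, but it is a reason to keep the dropouts' data rather than to replace them.

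**Conclusion.** The point holds in a limited form. On its natural reading the replacement rule secures 40 in total and does not guarantee 20 per group. The imbalance is systematic only if the arms lose patients at different rates: about 17.5/22.5 at an assumed 30%/10%, and 16/24 at 40%/10%. The cost to the between-arm comparison is about 1% to 2% in standard error, so imbalance alone would not justify a change.

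What justifies it is the conflict with the trial's purpose. A pilot that asks whether daily intake is possible replaces those for whom it was not, and for month-6 withdrawals and urine exclusions it also discards their data. The article does not say that dropouts will go uncounted, so the claim is not that the information is certain to be lost. The retained set of 40, however, cannot show it. Replacements from month 6 on also fall outside the expected recruitment period and each need a year of follow-up, with no stated limit.

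**What to change.** In Randomization and blinding, replace the sentences on replacement and on removal of data with these statements:

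- 40 patients are randomised 1:1, 20 per group at randomisation.
- Recruitment closes at the 40th patient.
- No patient is replaced after randomisation.
- Data collected up to dropout are kept, and patients who fail the urine check stay in the data set.
- Dropout and non-adherence are reported by arm, out of all randomised patients, as a feasibility result.

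The fourth statement is essential. Ending replacement while still deleting data would only make both arms smaller.

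The change is to wording only. It makes 20 per group true at randomisation, ties the 3 to 4 month expectation to a fixed 40 patients, and fixes the end of the trial at one year after the 40th enters. The cost is that fewer than 40 patients complete 12 months; deaths would reduce that number in any case.
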